## Abstract

**Background:**

Intraoperative hypotension is associated with increased morbidity and mortality. Current treatment is mostly reactive. The Hypotension Prediction Index (HPI) algorithm is able to predict hypotension minutes before the blood pressure actually decreases. Internal and external validation of this algorithm has shown good sensitivity and specificity. We hypothesize that the use of this algorithm in combination with a personalized treatment protocol will reduce the time weighted average (TWA) in hypotension during surgery spent in hypotension intraoperatively.

**Methods/design:**

We aim to include 100 adult patients undergoing non-cardiac surgery with an anticipated duration of more than 2 h, necessitating the use of an arterial line, and an intraoperatively targeted mean arterial pressure (MAP) of > 65 mmHg. This study is divided into two parts; in phase A baseline TWA data from 40 patients will be collected prospectively. A device (HemoSphere) with HPI software will be connected but fully covered. Phase B is designed as a single-center, randomized controlled trial were 60 patients will be randomized with computer-generated blocks of four, six or eight, with an allocation ratio of 1:1. In the intervention arm the HemoSphere with HPI will be used to guide treatment; in the control arm the HemoSphere with HPI software will be connected but fully covered. The primary outcome is the TWA in hypotension during surgery.

**Discussion:**

The aim of this trial is to explore whether the use of a machine-learning algorithm intraoperatively can result in less hypotension. To test this, the treating anesthesiologist will need to change treatment behavior from reactive to proactive.

**Trial registration:**

This trial has been registered with the NIH, U.S. National Library of Medicine at ClinicalTrials.gov, ID: NCT03376347. The trial was submitted on 4 November 2017 and accepted for registration on 18 December 2017.

**Electronic supplementary material:**

The online version of this article (10.1186/s13063-019-3637-4) contains supplementary material, which is available to authorized users.

## Background

Worldwide, an estimated 313 million people have to undergo surgical procedures every year [1]. Intraoperatively, patients often suffer from episodes of hypotension. Hypotension, defined as a mean arterial pressure (MAP) < 65 mmHg, occurs in 65% of surgeries [2]. Intraoperative hypotension is usually caused by anesthetics, pre-operative use of medication, existing comorbidities or by the surgery itself [3].

Since both pressure and flow are required to deliver oxygen to the tissues, hypotension can negatively affect organ function [4]. Clinical cohort studies and one randomized controlled clinical trial have shown intraoperative hypotension to be associated with postoperative complications such as myocardial ischemia, renal insufficiency and increased mortality [5–11]. Not only the time spent in hypotension but also the severity (the depth) of hypotension may be important for postoperative outcome [12]. The time-weighted average (TWA) combines the time and depth of hypotension [13, 14].

Hypotension is most often preventable; however, current management of the hypotensive episodes is predominantly reactive and often occurs with some delay. Machine learning was used to develop an algorithm to predict hypotension minutes before the blood pressure actually decreases, the Hypotension Probability Indicator (HPI) [15]. The HPI algorithm is developed using continuously measured waveform data from 1334 patients, internally validated on a cohort of 350 patients and externally validated on a cohort of 204 patients. The HPI algorithm is able to predict hypotension with 88% sensitivity and 87% specificity minutes before a hypotensive event occurs [15].

We hypothesize that the use of the HPI algorithm in combination with a personalized treatment protocol will reduce the amount of time spent in hypotension measured by the TWA during non-cardiac surgery.

## Methods/design

### Study design

This investigator-initiated trial is divided into two phases. Phase A consists of prospective data collection in 40 patients to gain insight into the normal TWA in our study population. Phase-A data are collected to check our sample size for phase B and to verify if the control group is a representative sample. Phase B is a single-center, randomized controlled (1:1), superiority trial including 60 patients. The study takes place in the Academic Medical Center (AMC) Amsterdam, The Netherlands, a tertiary academic center. The study started with inclusion of the first patient in November 2017, the planned duration of the trial is 18 months. This trial has been registered with the NIH, U.S. National Library of Medicine at ClinicalTrials.gov (NCT03376347). This manuscript was written in accordance with the Standard Protocol Items: Recommendations for Interventional Trials (SPIRIT) guideline (Additional file 1) on reporting of intervention trial protocols [16].

### Eligibility criteria

Adult patients (aged 18 years or older) scheduled to undergo an elective, clinical, non-cardiac, surgical procedure under general anesthesia and requiring an arterial line will be eligible for inclusion. A desired target MAP of 65 mmHg during surgery is used as an inclusion criterion, to ensure that both study arms will be similar in this aspect. Patients undergoing emergency surgery are not eligible. Patients with cardiac failure, severe cardiac shunts, severe aortic stenosis and severe cardiac arrhythmias will be excluded in accordance with the summary of product characteristics of the HPI algorithm. Patients enduring significant hypotension before surgery and patients requiring dialysis will be excluded. Patients planned to undergo liver surgery or vascular surgery will be excluded because of the use of vascular clamping. For this trial, anesthesiologists are not allowed to use a different hemodynamics treatment protocol besides our study protocol; therefore, an exclusion criterion is the planned usage of a perioperative Goal Directed Fluid Therapy (GDFT) protocol.

Researchers will screen all patients presenting for elective, non-cardiac, non-day-case surgery. Patients will be contacted and informed in case of eligibility. Patient informed consent will be obtained the day prior to surgery.

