### Statistical analyses

We will analyze the data based on an intention-to-treat principle. The intention-to-treat population is defined as all patients who meet the inclusion criteria at the end of the study period.

Continuous data will be presented as median with range and/or interquartile range (IQR), or mean with standard deviation and range when normally distributed. Normality of distribution will be assessed visually with histograms and Q-Q plots. Categorical data were given as frequencies with percentages. For each of the analyses a probability value of *p* < 0.05 will be considered statistically significant.

Our primary outcome is TWA in hypotension (phase B). We will compare the TWA of each arm using the Student’s *t* test or Mann-Whitney *U* test, depending on the distribution of the data. The baseline data collection enables us to calculate the normal TWA spent in hypotension in our hospital and will be used to verify the representativeness of our control group. We will compare the TWA in the baseline group (phase A) to the TWA in the control arm (phase B).

The secondary and exploratory research questions involving categorical data will be analyzed using the *χ*^2^ test/Fisher’s exact test and secondary research questions involving continuous (numerical) data will be analyzed using the Student’s *t* test or the Mann-Whitney *U* test. Feasibility of working with HPI will be analyzed using qualitative research methods, reporting the number of protocol violations with reasons. Underlying causes of intraoperative hypotension will be analyzed using our study flowchart (Fig. 2) on all 100 patients. To assess whether use of HPI intraoperatively results in less postoperative hypotension at the PACU the TWA in hypotension during PACU stay will be analyzed. The exploratory questions will not be addressed in the primary article. All analyses for the primary article will be done using Matlab (R2018b) and SPSS (version 25).

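### The intention-to-treat set is fixed by an end-of-study eligibility judgement, against inclusion criteria that the article states inconsistently, and not by randomisation

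*Protocol article*

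**What the plan says.** Three parts of the protocol article bear on who is analysed.

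- **Statistical analyses.** After committing to the intention-to-treat principle, it states: "The intention-to-treat population is defined as all patients who meet the inclusion criteria at the end of the study period". The definition mentions neither randomisation nor allocated arm.
- **Abstract, Methods/design.** The patients to be included have "non-cardiac surgery with an anticipated duration of more than 2 h, necessitating the use of an arterial line". The pressure condition there is worded differently from the one in the eligibility section: "an intraoperatively targeted mean arterial pressure (MAP) of > 65 mmHg".
- **Eligibility criteria.** Patients having an elective "surgical procedure under general anesthesia and requiring an arterial line will be eligible for inclusion", with no minimum duration. On pressure: "A desired target MAP of 65 mmHg during surgery is used as an inclusion criterion", for the stated reason that the arms should be alike in this respect. On screening: "Researchers will screen all patients presenting for elective, non-cardiac, non-day-case surgery", again with no duration.

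Separately, the section Sample size calculation (phase B) allows randomised patients to be excluded and replaced for three reasons: no measurement begun, no arterial line placed, or device failure that prevented data collection. Duration and target MAP are not among them.

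**The concern.** An intention-to-treat set is meant to be closed at randomisation, so that nothing learned afterwards can change who is counted. Here the set is closed by asking, at the end, who met the inclusion criteria. Followed as written, that permits a randomised patient with a recorded outcome to be dropped. Exclusions made after randomisation are not protected by it and can differ between arms.

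The inconsistent criteria make this worse. A rule that sends the analyst back to the inclusion criteria needs one list of them, and the article gives two descriptions that do not match. Both items bear on the primary outcome. Operation time is the denominator of the time-weighted average (TWA), and the 65 mmHg in the pressure criterion is also the threshold below which hypotension is counted.

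**Working it through.** **1. The two descriptions side by side**

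| Item | Abstract, Methods/design | Eligibility criteria |
|---|---|---|
| Anticipated duration | more than 2 h | not stated |
| Target MAP | above 65 mmHg | 65 mmHg |
| Arterial line | yes | yes |

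No other section shown states a duration criterion or reconciles the two MAP wordings.

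**2. What the analysis rule does with them**

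Take a randomised patient with a planned 90-minute operation, an arterial line and a complete recording.

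- Under the exclusion-and-replacement rule in the sample size section, the patient stays, because none of the three reasons applies.
- Under the intention-to-treat definition with the Eligibility criteria section, the patient is in.
- Under the same definition with the abstract's description, the patient is out.

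The same data can therefore give two analysis sets. Even with a single list, the definition would still remove any randomised patient later judged ineligible.

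**3. The article's own sample size**

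Inputs from Sample size calculation (phase B): difference 0.38, SD 0.51, two-sided alpha 0.05, 80% power, two-group t test.

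- Effect size: 0.38 / 0.51 = 0.745 (the article gives 0.74).
- Noncentral t at 0.74: 29.66 per group, so 30. Power at 30 per group is 80.5%.

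The figure reproduces, and neither duration nor target MAP enters it.

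**4. Illustration: one short case**

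The example under Outcome measures has MAP 50 for 5 min, so the area is 15 × 5 = 75. Assume that the area stays at 75 when the operation is shorter.

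- 120 min: 75 / 120 = 0.625
- 60 min: 75 / 60 = 1.25
- Change for that patient: 1.25 − 0.625 = 0.625
- Change in a 30-patient arm mean: 0.625 / 30 = 0.021, which is 0.021 / 0.38 = 5.5% of the target difference
- Two such patients in the same arm: 2 × 0.625 / 30 = 0.042, or 11%

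If the area instead accrues in proportion to time, 60 min gives 37.5 / 60 = 0.625, and nothing changes.

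**5. Illustration: patients dropped**

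Assume that k patients per arm are removed as ineligible and not replaced, with the effect size still 0.74. The documents do not give k.

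| k per arm | n per arm | Power |
|---|---|---|
| 0 | 30 | 80.5% |
| 1 | 29 | 79.1% |
| 2 | 28 | 77.6% |
| 3 | 27 | 76.1% |
| 5 | 25 | 72.7% |

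**The case against.** **The eligibility texts may not conflict.** A reader might infer that they contradict each other outright and admit two different populations. The documents do not go that far. On duration, one text states a criterion and the other is silent; no section says that shorter operations are admitted, and both texts can be met by applying every condition listed. The screening sentence describes who is looked at, not who is enrolled. On MAP, 65 and above 65 can both mean keeping pressure above the hypotension threshold. This stands. What remains is that the section meant to define eligibility omits a condition that the abstract includes.

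**The definition may only be loosely worded.** It could mean all eligible patients accrued by the time the study closes, and planned duration and desired target are fixed before surgery. Randomization and blinding also has an independent researcher, blinded to allocation, carry out the primary analysis. This reduces the risk but does not remove it. On either reading, membership rests on meeting criteria and not on having been randomised. Blinding of the analyst is stated for the analysis; the article does not extend it to an end-of-study eligibility judgement.

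**The numerical effect is small.** A reader might set the 0.625 shift in step 4 against the target difference of 0.38 and conclude that one or two short cases could overturn the result. That compares one patient's value with a difference between group means. The arm mean moves by about 0.02 per case, and only if the area is held fixed. Randomisation spreads such cases over both arms, and the plan allows a Mann-Whitney test if the data are not normal. The criterion also concerns anticipated duration, so a case planned for over 2 h that finishes early is eligible under both texts. This objection stands in full.

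**Conclusion.** The point holds as a fault in the definition of the analysis set, aggravated by inconsistent criteria. As written, the intention-to-treat population depends on eligibility judged at the end of the study, contrary to the principle that the same section invokes. This would need correcting even if the two eligibility texts agreed. Their mismatch (an omitted duration, and a MAP difference that may be wording only) adds uncertainty about which list applies.

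The effect on the result cannot be quantified, because the documents do not say how many randomised patients might be affected or in which arm. The arithmetic gives scale only: about 0.02 on an arm mean for one 60-minute case with the area fixed at 75, and power of 76.1% instead of 80.5% if three per arm were dropped without replacement. The documents do not show that short cases inflate TWA, or that patients with higher targets spend little time below 65 mmHg. The sample size of 30 per arm is not in question.

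**What to change.** 1. In Statistical analyses, define the primary analysis set as all patients randomised in phase B, analysed in their allocated arm, with no exclusion on eligibility judged after randomisation.
2. Report separately, by arm and with reasons, any randomised patients without outcome data under the exclusions in Sample size calculation (phase B).
3. Reconcile the abstract and the Eligibility criteria section into one list. It should say whether an anticipated duration is required and give one wording of the target-MAP criterion. Which duration or target is right is for the investigators to settle.
4. State that eligibility is judged only on facts known before randomisation, so on anticipated and not actual duration.

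The cost is wording only, with no extra patients, measurements or change to the sample size.

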### Study outline

Patients will be contacted on the surgical ward or at the pre-operative assessment clinic, and written information and oral explanation will be provided. Patient characteristics, medical history, medication use and American Society of Anesthesiologists (ASA) physical score classification will be collected from the medical records. Blood pressure measured at the outpatient clinic, blood pressure measured the day before surgery on the ward and blood pressure measured in the operating theater before induction will also be registered.

Phase A: TWA and normal treatment behavior of anesthesiologists in the AMC will be collected prospectively as baseline data. These data will be used to verify our sample size calculation for phase B and to study whether our control group is representative for the study population by comparing the baseline group versus the control group. During this phase of the study the treating anesthesiologist and anesthesia nurse will not be informed about the aim of the study or the endpoints measured.

Phase B: in this phase, patients will be randomized. The treating anesthesiologist and the anesthesia nurse will be informed about the study protocol and the usage of the HPI algorithm (with the secondary screen) the day before the surgery. All study interventions are to be performed by trained study personnel or the treating anesthesiologist, following instructions from the researchers.

In both study phases a researcher will be present – continuously – during all surgeries to note surgical and anesthetic details.

For a Consolidated Standards of Reporting Trials (CONSORT) flow diagram of the study see Fig. 1. All data will be entered using an electronic Clinical Report Form build in Castor EDC, a Good-Clinical-Practice-compliant data management system [17].

**Fig. 1 Fig1:**
[figure not shown]
Consort Flow diagram

### Randomization and blinding

In phase B, patients will be randomized to either use of the HPI algorithm intraoperatively (intervention arm) or standard care (control arm). We will use a computer-generated, permutated block randomization, with a 1:1 allocation ratio. This will result in concealed and varying permutated block sizes of four, six or eight patients.

Randomization will be performed by a designated researcher. An independent researcher (not involved in collecting study data), blinded for the randomization, will perform the statistical analysis for the primary outcome.

### Study procedures and interventions

The HPI algorithm was previously internally and externally validated [15]. The HPI algorithm is only available on the HemoSphere and Flotrac monitoring systems and requires the use of a FlotracIQ sensor connected to an arterial line (Edwards Lifesciences Corp., Irvine, CA, USA). The FlotracIQ sensor has a splitter which enables the splitting of the arterial blood pressure signal to facilitate a blood pressure signal on both the Philips monitor (standard care) and the HemoSphere monitor (study).

In all study participants this system will be connected to both the HemoSphere and the Philips monitor. The Philips monitor displays the MAP, systole, diastole and the pulse pressure variation as per standard care protocol in our hospital. In the baseline group (phase A) and in the control arm (phase B) the HemoSphere with HPI software will be connected; however, the screen will be fully covered. In the control arm the anesthesiologist solely uses the variables visible on the Philips monitor to guide hemodynamic treatment. In the intervention arm the HemoSphere with HPI software will be visible and the perioperative hemodynamic management will be based on both the Philips monitor and the HemoSphere monitor. Use of the HPI software is additional to standard care, it is not used as a replacement of standard care. In the intervention arm we will ask the anesthesiologist and anesthesia nurse to use the study treatment flowchart (Fig. 2). If the HPI alarm goes off, which entails both a sound and a flickering light, we ask the anesthesiologist to act upon this alarm preferably within 2 min. Use of the study treatment flowchart ensures that the anesthesiologist has to think about the underlying cause. The HemoSphere with HPI software has a second screen (Fig. 3) with variables that provide information about the underlying cause of the predicted hypotension (http://ht.edwards.com/scin/edwards/eu/sitecollectionimages/edwards/eu%20hpi%20brochure_digitalversion_largerfile%20for%20online%20use_10-6.pdf).

**Fig. 2 Fig2:**
[figure not shown]
HYPE personalized treatment guidance protocol. HPI=hypotension prediction index. MAP= mean arterial pressure. EaDyn= dynamic arterial elastance. SVR= systemic vascular resistance. SVV= stroke volume variation. SV=stroke volume. dP/dT= delta pressure/delta time, measure for left ventricular function

**Fig. 3 Fig3:**
[figure not shown]
HemoSphere with HPI and secondary screen. P↓BP= probability of hypotension, this is a prediction ranging from 0-100%. MAP= mean arterial pressure. CO= cardiac output. SVR= systemic vascular resistance. PR= pulse rate. SV= stroke volume. SVV= stroke volume variation. dP/dt= delta pressure/delta time. Eadyn= dynamic arterial elastance

### Outcome measures

Our primary outcome measure is the TWA in hypotension during surgery. The TWA is a calculation of the depth (in millimeters of mercury) of hypotension below the “threshold” MAP of 65 mmHg multiplied by the time spent in hypotension in minutes, this results in an area under the threshold AUT, see Fig. 4. To better compare this value between different operations this AUT will be divided by the total duration of the operation:

**Fig. 4 Fig4:**
[figure not shown]
AUT and AAT calculations. **a** demonstrates the calculation of the area under (AUT) the curve used to calculate the TWA in hypotension. *TWA= (depth hypotension below MAP 65 threshold in mmHg x time spent below MAP 65 threshold in minutes, the AUT) / total duration operation in minutes)*. **b** and 4**c** demonstrate the calculation area above the curve (AAT) used to calculate the TWA in hypertension and the TWA of HPI alarm

$$ \mathrm{Time}\ \mathrm{weighted}\ \mathrm{average}=\frac{\mathrm{depth}\ \mathrm{of}\ \mathrm{hypotension}\times \mathrm{time}\ \mathrm{spent}\ \mathrm{in}\ \mathrm{hypotension}}{\mathrm{total}\ \mathrm{surgery}\ \mathrm{time}} $$

Example: a MAP of 50 mmHg for 5 min results in an AUC of 75 (15 × 5). The total duration of the operation in minutes is 120 min. TWA = 75/120 = 0.625.

Hypotension is defined as a MAP < 65 mmHg for 1 min. An HPI alarm is defined as an HPI value of 85% and above during at least 1 min. A subsequent hypotensive episode, as well as an HPI alarm only counts as two separate events when respectively the MAP or the HPI will be normal for at least 1 min.

The secondary outcome measures include incidence of hypotension, time in hypotension, the percentage of time in hypotension and the AUC of a MAP < 65 mmHg. The above-mentioned parameters including TWA will also be assessed for hypertension (defined as MAP > 100 mmHg for at least 1 min) and for the HPI alarms. For hypertension and HPI alarm the area above the curve (AAT) will be calculated instead of the AUC, see Fig. 4. We will assess the treatment behavior of hypotension and HPI. This includes treatment choice (i.e., vasopressors, fluids, inotropes, position changes), treatment dose, time to treatment and feasibility of working with HPI based on the number of protocol violations.

Exploratory outcomes include underlying cause(s) of intraoperative hypotension and we will assess whether the use of HPI intraoperatively will result in less hypotension (measured in TWA) postoperatively at the Post Anesthesia Care Unit (PACU).

For an overview of the outcome assessments see Fig. 5.

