### Treatment behavior

For a machine-learning algorithm-based tool to help prevent intraoperative hypotension the treating anesthesiologists need to be willing to change their treatment behavior from reactive to proactive. Furthermore, the anesthesiologists will need to get used to diagnosing the underlying cause of hypotension based on the extra hemodynamic variables.

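### Time to treatment counted from hypotension exists only for episodes the intervention failed to prevent; the between-arm comparison should start at the HPI alarm and keep untreated alarms

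*Protocol article*

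**What the plan says.** The protocol article, Outcome measures (text after Fig. 4), lists treatment behavior as a secondary outcome for two kinds of event: "We will assess the treatment behavior of hypotension and HPI. This includes treatment choice". The components include "treatment dose, time to treatment and feasibility of working with HPI based on the number of protocol violations". Each kind of event is defined there: "Hypotension is defined as a MAP < 65 mmHg for 1 min" and "An HPI alarm is defined as an HPI value of 85% and above during at least 1 min".

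Statistical analyses gives one rule for outcomes of this type: "secondary research questions involving continuous (numerical) data will be analyzed using the Student’s *t* test or the Mann-Whitney *U* test".

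Study procedures and interventions gives the arms different triggers. In the intervention arm, "we ask the anesthesiologist to act upon this alarm preferably within 2 min". In the control arm the HemoSphere is connected but covered, and staff work from the Philips monitor alone. The Discussion (Treatment behavior) says that for such a tool to help, "the treating anesthesiologists need to be willing to change their treatment behavior from reactive to proactive".

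**The concern.** The intervention is designed to bring treatment forward, ahead of the fall in MAP. Where it works, no hypotensive episode follows and there is no onset from which to time treatment. The onset-based times left in the intervention arm come from alarms that were missed, answered late or treated without success. In the control arm, where staff do not see the alarm, most episodes still contribute. The two sets of episodes are no longer comparable by randomization, and this would be so even with one event per patient.

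The alarm-based part has a different gap. An alarm that ends without treatment has no time to treatment, so a t or Mann-Whitney test on observed times omits it. Such alarms may be more frequent in the control arm, where nobody can see them.

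At stake is a secondary measure that bears on whether treatment really moved from reactive to proactive. A reader could see no difference, or a slower intervention arm, when treatment had in fact come earlier.

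**Working it through.** **The plan's own figure.** The article states none for time to treatment. Its only related figure, the sample size for the primary outcome, reproduces and is not at issue: 0.38/0.51 = 0.745, stated as 0.74, and 30 per arm gives two-sample t-test power of 0.805.

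**Illustration 1.** All inputs are assumptions; none comes from the article.
- The time from alarm to hypotension, if untreated, is exponential with mean *l* = 3, 5 or 10 min.
- In the intervention arm a share *p* = 0.5 or 0.8 of alarms is acted on, with exponential delay of mean 2 min. Treatment before onset averts the episode.
- All other treatment follows onset, with exponential delay of mean 2 min in control and 2*s* min in intervention (*s* = 1 or 1.5).

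Formulas:
- Episodes averted: *p* × *l*/(*l* + 2).
- Alarms acted on, but only after onset: *a* = *p* × 2/(*l* + 2).
- Mean time from onset, intervention: [2*a* + 2*s*(1 − *p*)] / [*a* + (1 − *p*)]. Control: 2.
- Mean time from alarm, intervention: 2*p* + (1 − *p*)(*l* + 2*s*). Control: *l* + 2.

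Worked case, *l* = 3, *p* = 0.5:
- Averted: 0.5 × 3/5 = 0.30, and *a* = 0.5 × 2/5 = 0.20.
- From onset, *s* = 1: (0.40 + 1.00)/0.70 = 2.00 min.
- From onset, *s* = 1.5: (0.40 + 1.50)/0.70 = 2.71 min.
- From alarm: 1 + 0.5 × 5 = 3.5 min (*s* = 1) or 1 + 0.5 × 6 = 4.0 min (*s* = 1.5), against 5.0 min in control.

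| *l* | *p* | Averted | From onset, *s* = 1 / 1.5 (control 2.00) | From alarm, *s* = 1 / 1.5 | Control from alarm |
|---|---|---|---|---|---|
| 3 | 0.5 | 30% | 2.00 / 2.71 | 3.5 / 4.0 | 5.0 |
| 3 | 0.8 | 48% | 2.00 / 2.38 | 2.6 / 2.8 | 5.0 |
| 5 | 0.5 | 36% | 2.00 / 2.78 | 4.5 / 5.0 | 7.0 |
| 5 | 0.8 | 57% | 2.00 / 2.47 | 3.0 / 3.2 | 7.0 |
| 10 | 0.5 | 42% | 2.00 / 2.86 | 7.0 / 7.5 | 12.0 |
| 10 | 0.8 | 67% | 2.00 / 2.60 | 4.0 / 4.2 | 12.0 |

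A simulation of 400,000 events agrees to within about 0.02 min. The equality at *s* = 1 follows from the exponential delays, which have no memory: a delay that has outlasted onset starts afresh.

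**Illustration 2.** This also uses assumed inputs: lead time uniform on 3 to 10 min (mean 6.5), 2 min for treatment to work, 20% of alarms missed, exponential reactions.
- Mean reaction, with 30% slow teams (5 min) and 70% others (2 min): 0.3 × 5 + 0.7 × 2 = 2.9 min.
- From alarm: control 6.5 + 2.9 = 9.4 min; intervention 2.9 + 0.2 × 6.5 = 4.2 min.
- From onset, among episodes treated after onset, all teams alike: 2.89 (intervention) v 2.91 min (control).
- With slow teams and misses spread equally: 3.31 v 2.91 min. Across the variants with slow teams examined: about 3.1 to 4.0 v 2.9 min.
- Same equal-miss case, counting treatment before onset as time zero: 2.53 v 2.91 min, so the sign changes.

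Both illustrations show that the onset-based contrast does not follow the true change in timing, and that its sign depends on team mix and counting rule. The alarm-based contrast favors the earlier-treating arm throughout.

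**The case against.** The strongest reply is that the article does not confine time to treatment to hypotensive episodes. A reader might infer that it does, and that every averted episode is lost. The outcome sentence names HPI alarms as well, alarms have their own definition, and the device is connected in both arms. An averted episode preceded by an alarm is therefore within the outcome. This stands, and the stronger reading fails.

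A reader might also infer that the plan will show the intervention arm as slower. The article does not support this either. Every input above is assumed; with homogeneous teams the result is no difference, and a reversal needs slow responders to predominate among the remaining episodes.

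A further reply is that clock start, untreated alarms and negative times are details for the full protocol or SAP, and that the test rule is generic. It is true that the article does not mention time to treatment in that rule, and missing detail is no finding. But time to treatment is a named, continuous secondary outcome and the rule as worded covers it. The point is that this stated test does not suit this outcome.

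Finally, an alarm-based analysis has limits of its own. Later alarms are shaped by earlier treatment, stopping the clock when an alarm resolves untreated may be informative, and control staff cannot see the alarm. These are fair, and the fix has to meet them.

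**Conclusion.** The concern holds in limited form. The hypotension-onset part of time to treatment is conditional on a post-randomization event that the intervention is meant to prevent, so a between-arm t or Mann-Whitney test on it is not a fair randomized comparison. That rests on the design alone. In the HPI part, alarms that end untreated have no time and would be lost from the same tests.

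The size cannot be estimated from the article. Under the stated assumptions the onset-based measure ranges from hiding the earlier treatment to showing the intervention arm up to about 0.9 min slower in the first illustration (2.86 − 2.00) and about 1.1 min slower in the second (4.0 − 2.9).

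The consequence is confined to a secondary measure. The primary TWA and the incidence of hypotension count averted episodes as benefit and are not affected.

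**What to change.** - Make the between-arm comparison in phase B the time from the HPI alarm to first treatment, using the article's own alarm definition (HPI of 85% or above for at least 1 min).
- Take each patient's first alarm as the main contrast, since later alarms are affected by earlier treatment. Include alarms not followed by hypotension.
- Use a time-to-event analysis that keeps untreated alarms. Handle resolution of the alarm without treatment as a competing event, or check it in a sensitivity analysis.
- Add, by arm, the proportion of first treatments given before MAP falls below 65 mmHg.
- Report times from hypotension onset within each arm as description only, without a between-arm test.
- State that control staff cannot see the alarm that starts their clock, so the contrast measures the effect of showing the alarm together with the treatment flowchart.

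The cost is wording and analysis programming. The HemoSphere is connected in both arms, and a researcher is present throughout surgery to note anesthetic details, so no new data collection should be needed. The sample size does not change.
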